## Abstract

**Background:**

Problem drinking, particularly risky single-occasion drinking is widespread among adolescents and young adults in most Western countries. Mobile phone text messaging allows a proactive and cost-effective delivery of short messages at any time and place and allows the delivery of individualised information at times when young people typically drink alcohol. The main objective of the planned study is to test the efficacy of a combined web- and text messaging-based intervention to reduce problem drinking in young people with heterogeneous educational level.

**Methods/Design:**

A two-arm cluster-randomised controlled trial with one follow-up assessment after 6 months will be conducted to test the efficacy of the intervention in comparison to assessment only. The fully-automated intervention program will provide an online feedback based on the social norms approach as well as individually tailored mobile phone text messages to stimulate (1) positive outcome expectations to drink within low-risk limits, (2) self-efficacy to resist alcohol and (3) planning processes to translate intentions to resist alcohol into action. Program participants will receive up to two weekly text messages over a time period of 3 months. Study participants will be 934 students from approximately 93 upper secondary and vocational schools in Switzerland. Main outcome criterion will be risky single-occasion drinking in the past 30 days preceding the follow-up assessment.

**Discussion:**

This is the first study testing the efficacy of a combined web- and text messaging-based intervention to reduce problem drinking in young people. Given that this intervention approach proves to be effective, it could be easily implemented in various settings, and it could reach large numbers of young people in a cost-effective way.

**Trial registration:**

Current Controlled Trials ISRCTN59944705.

## Background

Alcohol use is a major cause of the disease burden in most countries of the world [1]. In adolescents and young adults of developed countries, alcohol use constitutes the greatest risk factor for mortality and morbidity [2]. Problem drinking is associated with multiple social and interpersonal problems such as arguing with friends and parents, engaging in unplanned sexual activity, drinking and driving, assault, getting into trouble with the law, academic difficulties, unintended injuries, and suicidal acts. In the long term, problem drinkers have an elevated risk of developing chronic diseases, e.g., heart and liver diseases or alcohol dependence [3–5].

Indicators of problem drinking are (1) a daily average consumption of three or more standard drinks for men, and two or more for women [6] and (2) risky single-occasion drinking (RSOD, also called binge drinking), defined as drinking 5 or more drinks on an occasion for men and 4 or more drinks for women [7]. The prevalence rates of RSOD are particularly high in adolescence and young adulthood [8]. In Switzerland, the prevalence of at least monthly RSOD is 28% in adolescents ages 15 to 19 and 42% in young adults ages 20 to 24 [9]. Compared to RSOD, the prevalence of an increased mean daily consumption in adolescence and young adulthood is relatively low (2% at ages 15 to 19 and 3% at ages 20 to 24) and it always occurs in combination with RSOD [9].

Studies testing the efficacy of interventions to reduce problem drinking among adolescents were predominantly conducted in non-European countries and were targeted to college or university students [10]. Within this target group, individual interventions using motivational interviewing [11] or personalized normative feedback based on the social norms approach [12] were effective to reduce alcohol consumption and alcohol related problems [13].

While interventions based on motivational interviewing are typically provided in face-to-face counselling sessions, social norms interventions were mostly provided via computer generated tailored letters or web-feedback. Social norm refers to our perceptions and beliefs on what is “appropriate” or “normal” behaviour of people close to us. Alcohol use misperceptions, i.e. overestimations of the amount of alcohol consumed, have been found in several studies, primarily in samples of adolescents with higher educational background [12] but also in young people with heterogeneous educational levels [14]. The presentation of correct information about peer group drinking norms in a credible way is hypothesized to reduce perceived peer pressure for high levels of alcohol consumption in both problem drinkers and non-drinkers [12]. The effectiveness of social norms interventions to reduce alcohol misuse in university and college students was analysed in a Cochrane review [15]. This review concluded that normative feedback interventions delivered using the web or computer reduced drinking quantity, drinking frequency, and binge drinking in the short- and medium term.

Social norm interventions to reduce problem drinking typically consist of a single intervention session in which participants receive tailored web or printed feedback. Due to their length of up to 7–8 pages of text and graphics, these feedbacks are primarily suitable for individuals with higher educational level. To provide shorter and more recurrent feedback messages might not only be a more effective approach particularly for individuals with lower educational levels but also to support and maintain behaviour change over a longer time period. Mobile phone text messaging provides a suitable technology to deliver short and repeated messages. This service allows a cost-effective instantaneous delivery of short messages directly to individuals at any time and place. In the field of alcohol prevention, text messaging particularly allows the delivery of individualized messages at times when young people typically drink alcohol [16]. In Switzerland, as in most other developed countries, nearly all adolescents (95%) between the ages of 12 and 19 own a mobile phone and text messaging is the most commonly used mobile phone application [17].

Mobile phone text messaging is increasingly applied in the context of behaviour change interventions, particularly for smoking cessation and diabetes self-management [18, 19]. For alcohol treatment, two pilot studies based on small sample sizes are available. Suffoletto et al. [20] reported fewer heavy drinking days and fewer drinks per drinking day in 15 young adults reporting harmful alcohol use who received text messages supporting goal setting up to 3 months after emergency treatment. In a study using twice daily supportive text messages (n = 26) or a fortnightly thank you text message (n = 28) for 3 months, co-morbid depressive and alcohol dependent patients reported lower depression scores and a trend for higher cumulative abstinence duration [21].

Within a pre-post-study, the acceptance and initial efficacy of a combined, individually tailored web- and text messaging-based intervention program to reduce problem drinking in young people with predominantly lower educational level was tested [22]. This fully automated program provided (1) an online feedback about an individual’s drinking pattern compared to the drinking norms of an age- and gender-specific reference group and (2) recurrent individualized text messages over a time period of 3 months. The program was tested in 36 school classes at 7 vocational schools in Switzerland. Irrespective of their drinking behaviour, 477 apprentices who owned a mobile phone were invited to participate in the program. Of these, 364 (76%) participated in the program. The percentage of persons with RSOD significantly decreased from 76% at baseline to 68% at the 3-month follow-up assessment. Furthermore, a significant decrease in the percentage of persons with alcohol-related problems and in the mean number of standard drinks per week could be observed. Within this study protocol, we describe a randomised controlled trial testing the efficacy of an optimized version of this program, called *MobileCoach Alcohol,* within a controlled trial.

## Methods/design

### Design and hypotheses

A two-arm cluster-randomised controlled trial will be conducted to test the efficacy of the *MobileCoach Alcohol,* a combined web- and text messaging-based intervention to reduce problem drinking in young people. The efficacy of the intervention will be tested in comparison to an assessment only control group. The study participants will be assessed at baseline and at 6-month follow-up (Figure 1).

**Figure 1 Fig1:**
[figure not shown]
**Study design.**

### Participants, setting and procedure

The *MobileCoach Alcohol* will be tested in vocational and upper secondary school students due to (1) their heterogeneous educational level and (2) their age range, primarily between 16 and 20 years of age. In this age group, alcohol consumption increases considerably compared to younger age [9] and the use of Internet and mobile phone text messaging is widespread [17]. Vocational and upper secondary schools in the Swiss Cantons of Zurich and Berne will be invited by prevention specialist centres in Zurich and Berne to participate in the study.

The vocational and upper secondary school students will be invited for study participation during a regular school lesson reserved for health education. They will be invited by junior scientists to participate in a study testing innovative channels of information about alcohol consumption. To ensure sufficient participation and, thus, representativeness of the sample [23], a reward of 10 Swiss Francs for participation in the study at both baseline- and follow-up assessment will be announced. Each student will receive a tablet computer for conducting the screening, baseline assessment, and study registration. Inclusion criterion for study participation is possession of a mobile phone. After receiving informed consent, study participants will be invited to choose a username and to provide their mobile phone number. Participants of the intervention group will receive additional questions that are necessary for tailoring the intervention content. Subsequently, participants in the intervention group will receive an individualised feedback based on the social norms approach on their tablet computer. During the subsequent 3 months, participants of the intervention group will receive one or two individually tailored text messages per week to reduce problem drinking. Participants of the assessment-only group will receive no intervention. Computer-assisted follow-up assessments after 6 months will be conducted by a junior scientist, within the participating school classes, during regular school lessons and using tablet computers.

### Ethical review

The study protocol was approved by the Ethics Committee of the Philosophical Faculty of the University of Zurich, Switzerland (date of approval June, 24^th^, 2014). The trial will be executed in compliance with the Helsinki Declaration.

### Randomisation and allocation concealment

To avoid spill-over effects within school classes, we will conduct a cluster-randomised controlled trial using school class as a randomisation unit. Due to the heterogeneity of apprentices in the different vocational and upper secondary school classes (e.g. concerning gender or professions), we will use separate randomisation lists for each school (stratified randomisation). Furthermore, to approximate equality of sample sizes in the study groups, we will use block randomisation with computer generated randomly permuted blocks of 4 cases [24].

The junior scientists supervising the baseline assessment in the vocational schools will be blinded concerning group allocation of the school classes. Also, group allocation will not be released to study participants until having provided informed consent, their username, mobile phone number, and baseline data. Furthermore, the junior scientists conducting the computer assisted follow-up assessments will be blinded when assessing the primary and secondary outcome measures.

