### Sample size calculation

An estimation of the expectable effect size was based on the results of the pre-post study testing the initial efficacy of the program [22]. This study revealed a decrease in the percentage of persons with at least one RSOD occasion in the last month from 76% at baseline assessment to 68% at follow-up assessment. It is assumed that the improvements in the content and tailoring of the intervention will also result in an improved efficacy. Based on these considerations, it is assumed that the percentage of persons with at least one RSOD occasion in the last month at follow-up will be 76% in the control group and 66% or lower in the intervention group. A sample size of n = 322 in each study group would be required to have 80% power for a χ^2^-test (α = 5%, 2-sided) in order to detect this difference based on a calculation using *G-Power*
[25]. As students are nested within school classes, a potential design effect needed to be considered. Based on [22] an average cluster size of 10 study participants per school class and an intra-cluster correlation coefficient of 0.05 could be expected. This would result in a design effect of 1.45. Multiplying this design effect by the required size for an unnested sample (n = 322) results in a required sample size of n = 467 per study group and a total of n = 934 study participants.

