### Data analyses

Generalized Estimation Equation analyses (GEE) [41] will be used to test the efficacy of the intervention on the different outcome measures. Based on the scale level of the measurement and its distribution, logistic GEE-models, linear GEE-models or GEE-models for count variables will be applied. Potential baseline differences will be considered by adding additional baseline variables as covariates to the GEE-models. Both (1) complete case analyses (CCA) considering all study participants with available follow-up data and (2) intention to treat (ITT) analyses will be conducted. For the ITT analyses, the multiple imputations procedure (MICE) of STATA will be applied. Given the clustered nature of the data, robust variance estimators for all GEE-models will be computed, using the cluster option of STATA.

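### Randomisation is stratified by school, but the analysis neither names school nor has a covariate rule likely to select it, so the reported standard errors may be somewhat too large

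*Protocol article*

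**What the plan says.** The section on randomisation and allocation concealment sets out a cluster trial "using school class as a randomisation unit". Because classes differ, for instance in gender mix and profession, "we will use separate randomisation lists for each school (stratified randomisation"). Allocation uses "computer generated randomly permuted blocks of 4 cases".

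The section on data analyses plans logistic, linear or count GEE models according to the outcome. Baseline variables are to be added where baseline differences might matter. No variable is named, and school is neither named nor excluded. On variance it says that "robust variance estimators for all GEE-models will be computed, using the cluster option of STATA". It does not say whether the cluster is the class or the school.

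The sample size section assumes "an average cluster size of 10 study participants per school class and an intra-cluster correlation coefficient of 0.05 could be expected". It adds: "This would result in a design effect of 1.45". No reduction is made for stratification. The section on assessments and outcomes says that school and class characteristics are recorded at baseline, so the information is available.

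**The concern.** When randomisation is balanced within schools, differences between schools largely cancel out of the comparison of arms. A standard error computed from all variation between classes still counts those differences. It then overstates the uncertainty of an estimate that is more precise than reported.

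The stated covariate rule makes this more likely. It is triggered by differences between the arms at baseline, and separate blocked lists are there to prevent such differences by school. A variable that the design has balanced will seldom be picked by a rule that looks for imbalance, although the design is the reason to include it.

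At stake are intervals wider than they need to be and a type I error below the nominal 5%. The error is in the safe direction.

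**Working it through.** **Inputs from the article.** Ten participants per class, intra-cluster correlation (ICC) 0.05, "76% in the control group and 66% or lower in the intervention group", and "80% power for a χ^2^-test (α = 5%, 2-sided"). The pilot had 36 classes in 7 schools, about 5 per school.

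**Assumed, not given.** The part of the ICC shared by classes of the same school, called r below, is taken from 0 to 0.05. Several classes per school are also assumed.

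**The plan's own figure.** The pooled two-sided formula for 76% against 66% gives 322.02 per arm, and power at 322 is 0.79996. The design effect is 1 + 9 × 0.05 = 1.45. Then 322 × 1.45 = 466.9, so 467 per arm and 934 in total. All stated figures reproduce.

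**Effect of leaving school out.** With full balance within schools, the design effect that applies to the estimate is 1.45 − 10r. A class-clustered standard error without school still reflects 1.45. The ratio of reported to true interval width is therefore k = √(1.45 / (1.45 − 10r)), and the actual two-sided type I error is 2 × [1 − Φ(1.96k)].

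| r | True design effect | k | Actual type I error | Power, school omitted | Power, school included |
|---|---|---|---|---|---|
| 0 | 1.45 | 1.00 | 0.050 | 0.80 | 0.80 |
| 0.01 | 1.35 | 1.036 | 0.042 | 0.81 | 0.83 |
| 0.025 | 1.20 | 1.099 | 0.031 | 0.83 | 0.87 |
| 0.05 | 0.95 | 1.235 | 0.016 | 0.85 | 0.93 |

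Example of the power with school omitted, at r = 0.025: the true standard error is √[(0.76 × 0.24 + 0.66 × 0.34) / (467 / 1.20)] = √(0.4068 / 389.2) = 0.0323. Then Φ(0.10 / 0.0323 − 1.96 × 1.099) = 0.83.

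**Simulation on the risk-difference scale.** There were 3,000 runs per setting, with 12 schools × 8 classes, 18 × 5 and 31 × 3, and blocks of 4.

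- The class-clustered standard error, without school, was 0.98 to 1.02 times the true standard deviation at r = 0, about 1.06 to 1.07 at 0.025, and 1.07 to 1.15 at 0.04. The formula gives 1.10 at 0.025 and √(1.45 / 1.05) = 1.175 at 0.04.
- Part of that gap comes from incomplete blocks. With 5 classes a school is always split 3 to 2. In 18 such schools the school contribution is about 18 × (1/45)² = 0.0089r, against 4/90 = 0.0444r without stratification, so one fifth remains. At r = 0.025 the formula then gives √(1.45 / (1.45 − 0.8 × 0.25)) = √(1.45 / 1.25) = 1.077. The table is therefore nearer an upper limit.
- At 18 × 5 and r = 0.025, the estimates with and without school had the same true standard deviation, 0.0338. What differs is the reported error.
- Clustering the variance on school, with no school terms, brought the ratio to about 0.95 to 1.02, but the normal-based test then rejected in 5% to 9% of null trials.

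**Second simulation.** It used 19 schools × 5 classes × 10 students and 3,000 trials per setting. GEE without school was compared with a class-level regression with school effects and a t test. With a quarter of the ICC at school level, type I error was 4.7% against 5.2% and power 80.7% against 81.1%. With half, it was 3.3% against 4.5% and 79.7% against 83.7%. The Monte Carlo standard error is about 0.4 points for type I error and 0.7 for power, so only the second setting shows a clear effect.

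**The case against.** The strongest reply is that silence is not exclusion. The covariate list is open, this is a condensed article, and an analysis plan that is not shown may list the strata. That stands against any statement that the models omit school. It does not answer the narrower point: the article does state a principle for choosing covariates, and that principle follows chance imbalance, not the design.

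Second, the cluster level is not named, and clustering on school would remove most of the excess width. This also stands. Class remains the natural reading, because it is the unit of randomisation and the unit for which cluster size and ICC are given.

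Third, the size cannot be fixed from the article. The reason it gives for stratifying is heterogeneity of classes, which is not an estimate of variance between schools. The abstract puts the number of schools at about 93. Taken literally, with 934 / 10 ≈ 93 classes, that is one class per school, and stratification would then gain nothing.

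A reader might also infer that the precision bought by stratification is lost, or that the trial is underpowered. Neither is supported. The estimate still benefits from the balance, and the sample size takes the full design effect of 1.45, so power is at least 0.80 throughout the assumed range.

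Finally, the remedy can do harm if applied carelessly: school terms with an uncorrected robust variance gave a type I error of 7% to 8% in the second simulation. This is a reason to specify the correction, not to ignore the strata.

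**Conclusion.** The point holds as a conditional one. The covariate rule is poorly matched to the stratified design and should be changed. If school is omitted, the variance is clustered on class, and schools contribute several classes each, then intervals are 0% to 24% too wide for a school part of the ICC between 0 and 0.05. The excess is about 4% at 0.01 and 10% at 0.025, and somewhat less where blocks are incomplete. The top of the range needs all of the clustering to lie between schools, which is an extreme case. The consequence is a mildly conservative test. It cannot create a false claim of efficacy. The change is worth making, but the trial's validity does not depend on it.

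**What to change.** In the section on data analyses:

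- Include school, as the randomisation stratum, in the primary and secondary models by design, separately from the baseline-difference rule. Set a rule in advance for pooling schools with only one class, for example by canton and school type.
- State that the robust variance is clustered on class.
- Use a small-sample-corrected robust variance with a t reference on classes minus schools minus 1 degrees of freedom (for 93 classes in 18 schools, 93 − 18 − 1 = 74). A class-level analysis with school effects is an alternative.
- State the target effect. School terms make the logistic odds ratio conditional on school. If a marginal effect is wanted, derive it by standardisation.
- Reconcile the abstract's number of schools with the number of classes implied by the sample size section, since the value of stratification depends on classes per school.

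The cost is a few sentences and no new data, and the text should be settled before outcomes are examined by arm. The main downside is the dependence on the small-sample correction. There is also a small loss of precision if schools do not differ at all: with 31 schools of 3 classes and no school variance, the true standard deviation rose from 0.0349 to 0.0371, a factor of 0.0371 / 0.0349 = 1.06.

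### Fixed, published blocks of 4 on a separate list per school could let recruiting staff predict later classes, because the baseline session can show a class's arm: a conditional risk to allocation concealment

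*Protocol article*

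**What the plan says.** Under Randomisation and allocation concealment, the protocol article fixes three features of the allocation:

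- The unit is the class: "we will conduct a cluster-randomised controlled trial using school class as a randomisation unit".
- Lists are kept by school: "we will use separate randomisation lists for each school (stratified randomisation".
- The block size is a single published number: "we will use block randomisation with computer generated randomly permuted blocks of 4 cases". As the class is the unit, I read a case here as a class.

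The same section makes two statements about concealment. For staff: "The junior scientists supervising the baseline assessment in the vocational schools will be blinded concerning group allocation of the school classes". For students: "group allocation will not be released to study participants until having provided informed consent, their username, mobile phone number, and baseline data".

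Under Participants, setting and procedure, the article describes the session itself. Recruitment takes place in class: "They will be invited by junior scientists to participate in a study testing innovative channels of information about alcohol consumption". After consent and registration the arms diverge in the same lesson: "Participants of the intervention group will receive additional questions that are necessary for tailoring the intervention content", and then "participants in the intervention group will receive an individualised feedback based on the social norms approach on their tablet computer". Control classes get neither step.

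**The concern.** The two sections fit together only up to a point in each session. Staff can be blind to a class's arm when they invite its students. Once some rooms go on to further questions and graphical feedback and others do not, the arm can be seen by whoever is supervising. The rule on releasing allocation protects students in the class being recruited. It does not stop staff from working out the arm of the next class in the same school.

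A short fixed block turns that knowledge into prediction. With two classes per arm in every four, the earlier arms in a block constrain the later ones, and the size of the block is in print.

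What is at stake is who enters the trial. Participation is voluntary: in the preceding pre-post study (Background) 364 of 477 invited apprentices, 76%, took part. The primary outcome is self-reported drinking. If encouragement to join differed with an expected arm, the groups could differ at entry in a way that randomising classes would not correct.

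**Working it through.** **Number of classes.** The article gives no predictability figure, so the only figure of its own to reproduce is the size of the trial (Sample size calculation). The design effect is 1 + (10 − 1) × 0.05 = 1.45. Then 322 × 1.45 = 466.9, so 467 per group and 934 in total, as stated. At 10 participants per class, 934 / 10 = 93.4, or about 93 classes.

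**Classes per school.** This is not given for the trial. The pre-post study had 36 classes in 7 schools, 36 / 7 = 5.1. The Abstract gives about 93 schools. Read literally, that is 93.4 / 93, or about one class per school. As 93 is also the implied number of classes, schools may stand there for classes, but the article does not settle it.

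**Certainty within a block of 4.** Suppose an observer knows all earlier arms in the school and the order of the list. There are six equally likely sequences (I = intervention, C = control). The number of allocations already determined in each is:

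| Sequence | Determined |
|---|---|
| IICC | 2 |
| ICIC | 1 |
| ICCI | 1 |
| CIIC | 1 |
| CICI | 1 |
| CCII | 2 |

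The mean is 8 / 6 = 1.33 of 4, or 33.3%. By position, the first and second classes are never certain, the third is certain with probability 2 / 6 = 1/3, and the fourth always.

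**Best guess.** The chance of a correct guess is 1/2, 2/3, then 1/3 + (2/3 × 1/2) = 2/3, then 1. The mean is 2.833 / 4 = 70.8%, against 50% by chance.

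**By number of classes per school, fixed blocks of 4:**

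| Classes per school | Certain share | Correct guesses | Certain, of 93 classes |
|---|---|---|---|
| 1 | 0% | 50.0% | 0 |
| 2 | 0% | 58.3% | 0 |
| 3 | 11.1% | 61.1% | about 10 |
| 4 | 33.3% | 70.8% | about 31 |
| 5 | 26.7% | 66.7% | about 25 |
| 6 | 22.2% | 66.7% | about 21 |
| 8 | 33.3% | 70.8% | about 31 |

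The last column is the certain share times 93, for example 0.267 × 93 = 24.8.

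**Effect of varying the block size.** Here sizes 4 and 6 are drawn with equal probability, and the observer is assumed to know that these are the possible sizes:

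| Classes per school | Certain: fixed → mixed | Correct guesses: fixed → mixed |
|---|---|---|
| 4 | 33.3% → 1.3% | 70.8% → 65.4% |
| 5 | 26.7% → 5.0% | 66.7% → 64.3% |
| 6 | 22.2% → 7.5% | 66.7% → 67.2% |
| 8 | 33.3% → 5.9% | 70.8% → 66.8% |

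Mixing sizes removes most of the certainty but little of the guessing advantage, and none of it at six classes. The required sample size does not change.

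**The case against.** The case on the other side is substantial.

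- *Several links are not in the article.* It does not say that the same staff return to a school, in what order classes are visited, whether staff know the order of the list, or when a class is randomised relative to consent. It says outright that staff are blinded. All of this stands, and it makes the risk conditional. The release rule suggests that an allocation already exists before consent, but that is an inference.
- *The literal reading of the Abstract removes the problem.* With about 93 schools and about 93 classes there is nothing to predict. This stands as the lower end of the range. Against it, lists by school with blocks of 4 balance nothing if each school gives one class, so the design makes sense only with several.
- *The route to bias is narrow.* Whole classes are invited in a regular lesson, the study is described neutrally, the same reward is announced to all, and the only inclusion criterion is having a mobile phone. Staff have no stated discretion over individual eligibility, so bias would need them to vary their encouragement of a class. The 76% participation shows room for differential uptake but no evidence of it. This limits the likely size and does not remove the route.
- *Students are already protected until they have given baseline data.* That is true for disclosure to students. The rule does not say whether release waits for the whole class. If feedback appears as each student finishes, early finishers could reveal the arm while classmates are still answering.
- *A fixed block of 4 is ordinary practice, and list custody is a matter for the full protocol.* I agree, and the absence of those details is not the point here. The point is the combination of a small published block, lists by school and a session whose content shows the arm.

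**Conclusion.** The point holds as a conditional risk to allocation concealment at recruitment. It needs three things: several classes per school, staff who see or hear the arms of earlier classes, and staff who know the order of the list. The article's account of the session makes the second plausible, and it leaves the other two open.

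If all three hold, the share of classes whose arm is certain before invitation runs from 0% (one or two classes per school) through 11% (three) and 27% (five, close to the pre-post study) to 33% (full blocks). Out of about 93 classes that is 0 to about 31, with about 25 at five per school. These are upper limits, as they assume perfect knowledge of earlier arms.

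A reader might infer more: that the blinding of baseline staff demonstrably fails, that students consent after their class has been randomised, or that 31 classes are predictable. The documents support none of these. They do not give the timing of randomisation or the staffing, and 31 requires every school to fill its blocks. The improvement is worth making because it is cheap, not because bias has been shown.

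**What to change.** 1. Generate the per-school lists centrally with randomly varying block sizes, for example 4 and 6 mixed, and do not disclose the sizes to field staff.
2. Release a class's allocation from the system only when baseline entry for the whole class is closed. As varying the sizes does little against guessing, this step and central custody of the lists should go with it.
3. Limit the blinding statement for baseline staff to the period before that release, so that it agrees with the described session.
4. Reconcile the Abstract's number of schools with the roughly 93 classes implied by the sample size, and state the expected number of classes per school, since the size of the risk depends on it.

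The cost is a change to the list-generation script and to the release rule, plus a few sentences of text. The downside is slightly looser balance within schools that contribute few classes, where a block of 6 would often stay incomplete.
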